### Assessments

#### Quality of life assessment

Quality of life will be evaluated with the QLQ-C30 version 3.0 developed by the European Organization for Research and Treatment of Cancer [8]. The QLQ-C30 incorporates 5 functional scales (physical, role, cognitive, emotional, and social); 3 symptom scales (fatigue, nausea/vomiting, and pain); 6 single-items (dyspnea, insomnia, appetite loss, constipation, diarrhea, and financial difficulties); and a global health subscale. Scores will be transformed to a 0–100 scale, with 100 reflecting highest functioning, highest symptomatology or highest global health, according to each scale. The minimal clinically important difference (MCID) is at least 5 points to achieve a clinically significant improvement [48].

To complement this assessment, the Medical Outcomes Study 36-Items Short-Form Health Survey (SF-36) will also be used [43]. The French validated version [49] contains 8 scales: physical functioning, role limitations (physical), bodily pain, general health, vitality, social functioning, role limitations (emotional), and mental health, which may be gathered in 2 second-order factors consisting of a mental component summary and a physical component summary. For each dimension, item scores will be coded, totaled, and transformed to a 0–100 score where the lowest score of 0 will correspond to ‘least healthy’ and the highest score of 100 will correspond to ‘healthiest’, with an estimated MCID of 3 points [50].

#### Fatigue assessment

The Multidimensional Fatigue Inventory (MFI-20) includes 20 items divided into 4 dimensions in the French version versus 5 dimensions in the English version [51]: general/physical fatigue, mental fatigue, reduced activities and motivation. Each subscale will be normalized to a 0–100 score: high score indicating a high degree of fatigue with a MCID of 3 points [52].

#### Anxiety and depression assessment

Anxiety and depression will be evaluated with the Hospital Anxiety and Depression Scale (HADS), which has been validated to measure anxiety and depression without confounding somatic symptoms of physical disorders [53]. It contains 14 items divided into 2 subscales: HADS-Anxiety and HADS-Depression of which the MCID is estimated at 1.7 points [54]. For each subscale, cutoff scores ≤7 indicates no symptoms; 8–10 signifies suspect disorder; and ≥ 11 represents significant disorder.

#### Clinical status assessment

BP, infectious events, serious infectious events, relapses, deaths, and their reasons will be collected by a hematologist as part of the standard medical surveillance. Given that a low BMI is correlated with poor survival after HSCT, BMI will be used to monitor weight fluctuations as a function of height [55]. Specifically, the BMI reference value used will be the representative average BMI value in a general population from an industrialized country (approximately 25 ± 2.5 kg/m^2^) [56].

#### HRV level and cardiac coherence score

HRV will be recorded at rest using the noninvasive SymbioLine® plethysmograph pulse sensor over a 10-min period. The recommended body posture will be sitting with knees at 90°, feet flat on the floor, hands on thighs, palms facing upward and eyes closed according to standard measurement of the short-term HRV [57]. Patients will be asked to relax and breathe normally and will have to stay seated without speaking or making any movements.

The last 5 min of HRV recording will then be analyzed with *HRVanalysis,* a free software that analyzes RR intervals (https://anslabtools.univ-st-etienne.fr) [58]. We will collect indicators of HRV to estimate the HRV level and cardiac coherence score. The SDNN indicates the level of cardiac variability, with high SDNN corresponding to high variability. The cardiac coherence score in percentage is associated with a good cardiac coherence state [26].

#### Physical condition assessment

Physical function will be evaluated with a 6-min walk test [59] and 50-ft walk test at fastest speed [60]. Muscular strength will be estimated from grip strength measured with a dynamometer for which values are correlated to general muscle mass [61]. The MCID of 6-min walk test is estimated at 25 m [62] but no MCID is known for 50-ft walk test and grip strength in chronic patients. Stability will be measured with a single limb stance test (eyes open and closed) and flexibility will be evaluated on both the lower and upper body. All of these assessments have been previously tested in hematologic patients or in the elderly; they are adapted and feasible for our study population [63–65].

The APA instructor will administrate the Global Physical Activity Questionnaire (GPAQ) to evaluate daily activities. The French version of GPAQ is validated by the World Health Organization [66] and collects information about three domains of physical activities (activity at work, travel to and from places, and recreational activity) and sedentary behavior.

#### Satisfaction and adherence to the protocol

Patient satisfaction and participation rates at APA and HRVB sessions (including information about dropout and reasons for doing so) will be monitored over the course of the study to assess the interest among hematologic patients throughout these interventions.

### Evaluation times and implementation

The APACCHE protocol will include 5 evaluation sessions: an introduction about protocol and medical prescription (T0), patient screening and getting informed consent (T1), a mid-term evaluation after 6 weeks of intervention (T2), a final assessment at 12 weeks when the intervention concludes (T3), and a 12-week follow-up (T4) (Fig. 2). To ensure a high-quality and organized protocol and to coordinate the various staff members in the hematology unit, a care pathway will be implemented.

**Fig. 2 Fig2:**
[figure not shown]
Timeline of the APACCHE study

At T0, hematologists will deliver a brochure about the APA program and a briefing note regarding the protocol to potential participants. They will complete a dedicated form related to the medical prescription of the APA program including details about clinical status and specific recommendations for the APA instructor. Then, the APA instructor will contact interested patients to make a first appointment (T1).

At T1, the hematologist will obtain informed consent from the patients, and will proceed to the randomization. For study participants who will be included in the experimental group, a clear description about HRVB training will be given by the APA instructor.

At T1, T2, T3 and T4, quality of life, fatigue, anxiety and depression will be assessed by trained interviewers. Clinical status will be collected by the hematologist and HRV level, cardiac coherence score, and GPAQ will be measured by the APA instructor. Physical tests will be conducted only at T1, T2 and T3. (Table 1).

**Table 1 Tab1:**
[figure not shown]
Schedule of enrolment, interventions, and assessments from SPIRIT guidelines

### Data collection and statistical analysis

#### Sample size

Based on a large study among 2800 hematologic patients [6], we expect an additional increase of 5 points, with a standard deviation of 7 points, in the QLQ-C30 score of the experimental group (HRVB+APA) after the 12-week intervention. Due to an estimated 10% missing data rate and dropout rate (abandonment, death, loss of sight), we aim to include 70 patients in the protocol (Fig. 3). They will be randomly assigned to one of two treatment groups (HRVB+APA (*n* = 35) versus APA only (n = 35)). Sample size was calculated with PASS 11® software (power analysis and sample size) to show a significant difference in improvement of quality of life in the experimental group with an alpha level of 5% and a statistical power of 80%.

**Fig. 3 Fig3:**
[figure not shown]
Recruitment and randomized allocation group from the CONSORT 2010 flow diagram

#### Blinding and intervention assignment

The specificity of the HRVB and APA interventions will not allow for the use of double-blind assignments for the APA instructor and hematologists. However, we will establish a blinding on the questionnaire assessments for the trained interviewers to maintain a high level of evidence.

Randomization will be balanced in both groups, with a 1:1 allocation ratio, without stratification. The randomization list will be established by the statistician from the Methodology and Data Management Centre before the start of the research. Different sizes of randomization blocks will be used to leave the investigators blind to their size and to avoid predictable allocation. Randomized block sizes of 4,6,8 or 10 blocks will be performed on STATA®. The randomization list will then be imported into the CsRandom module of the Ennov Clinical® electronic case report form (eCRF), which the investigator will use to perform the randomization.

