### Interventions

#### APA program

The APA program will consist of supervised aerobic and resistance training at moderate intensity of 12–14 on the Borg scale, corresponding to 70–80% max heart rate [16]. It will be supervised by an APA instructor during 12 weeks with 1-h sessions twice a week. The intensity will be progressive, adapted to individual capacities and functional limitations of each patient. This intervention will be done in small groups to promote exchange and conviviality and to optimize the rates of participation and compliance. Each session will be composed of four sections: 5-min warm-up, 30-min aerobic training, 20-min resistance training, and 5-min cool-down. Warm-up will include soft joint movements to prevent injuries. Aerobic training could involve a walking protocol (Fig. 1) or step aerobic exercises. Resistance training will consist of circuit training with various muscular reinforcement exercises. Finally, there will be 5-min of stretching exercises for the cool-down.

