#### HRVB training

HRVB will include 10 supervised, 1-h sessions spread evenly over the course of the 12 weeks and will be supervised by the APA instructor in a dedicated room at the hospital. Sessions will consist of exercises using the Symbiofi® cardiac coherence software (SymbioCenter® technology, SymbioLine® Professional, SYMBIOFI, Loos, France) that provides various interactive workouts to control the rhythm and amplitude of respiration in order to achieve a cardiac coherence state with an elevated cardiac coherence score. To help patients achieve the cardiac coherence state, they will see their cardiac coherence score displayed on the screen along with a respiratory guide at 6 breaths/min and the feedback of HRV in real time (tachogram) from a plethysmograph pulse sensor.

The first two of the ten supervised sessions will provide exercises based on relaxation techniques to breathe consciously and focus on abdominal breathing. The following sessions will include interactive exercises with biofeedback reflecting cardiac coherence state. For example, a patient will see displayed on a screen a changing landscape from stormy to sunny weather according to the cardiac coherence score. The last HRVB sessions will include exercises that require more autonomy using only relaxing music and pictures. Each session will end with a 5-min HRV recording with respiratory guidance at 6 breaths/min to compare cardiac coherence scores from one session to the next.

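### Hematologists are left unblinded for a reason that fits the APA instructor but not them, so detection bias in the judgement-dependent secondary clinical outcomes is partly avoidable

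*Protocol article*

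**What the plan says.** All references are to the protocol article.

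- **Who is unblinded, and why.** The section Blinding and intervention assignment gives this reason: "The specificity of the HRVB and APA interventions will not allow for the use of double-blind assignments for the APA instructor and hematologists".
- **Who is blinded.** Same section: "we will establish a blinding on the questionnaire assessments for the trained interviewers to maintain a high level of evidence". Database and data monitoring adds that the interviewers' eCRF access is restricted because of this blinding.
- **Who delivers the interventions.** The APA program section says of that program: "It will be supervised by an APA instructor during 12 weeks with 1-h sessions twice a week". HRVB training says the biofeedback sessions "will be supervised by the APA instructor in a dedicated room at the hospital". At T1, under Evaluation times and implementation, for the experimental group "a clear description about HRVB training will be given by the APA instructor".
- **Who randomises.** Evaluation times and implementation, at T1: "the hematologist will obtain informed consent from the patients, and will proceed to the randomization". The list sits in an eCRF module, "which the investigator will use to perform the randomization".
- **Who records clinical outcomes.** The section Clinical status assessment assigns this task as follows: "BP, infectious events, serious infectious events, relapses, deaths, and their reasons will be collected by a hematologist as part of the standard medical surveillance". Evaluation times and implementation places this at T1, T2, T3 and T4.
- **How the outcomes are used.** The abstract lists blood pressure, progression-free survival, overall survival and BMI as secondary outcomes. Statistical analysis compares the groups by log-rank test on death and/or relapse and on survival free of serious infectious events.

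**The concern.** The article gives one reason for leaving two kinds of staff unblinded. For the instructor it is unavoidable. For the hematologists it is not explained by anything they do within the interventions, and the one route to the arm that the text describes is an administrative task that someone else could perform.

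This matters because the hematologists supply outcome data. Whether an infection counts as serious, and when a relapse is declared, involve clinical judgement. A blood pressure reading does so to a lesser degree. The Hypothesis and Discussion sections state the expected direction: better blood pressure and fewer infections, relapses and deaths with HRVB. A recorder who knows the arm could lean that way without intending to. The article names no blinded assessor or adjudicator for these outcomes.

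**Working it through.** The point has no figure of its own, so the check sets the sections against each other.

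**1. Does the stated reason fit each role?**
- *APA instructor:* supervises APA (APA program), supervises HRVB and monitors the home-practice logbook (HRVB training), and explains HRVB to the experimental arm (Evaluation times and implementation). Blinding is impossible and the reason fits.
- *Hematologist:* at T0, prescribes APA. This comes before randomisation and is common to both arms, so it does not reveal the arm. At T1, obtains consent and randomises. No section gives the hematologist a part in delivering either intervention. The reason does not fit by itself.

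**2. Does the protocol treat blinding of such staff as feasible elsewhere?** Yes. The interviewers meet the same patients, who know their arm, at T1 to T4, and are still to be blinded. Two tools already exist: eCRF access that varies by role (Database and data monitoring), and a request that HRVB patients not discuss the training during APA sessions (HRVB training). Neither is applied to the hematologists' assessments.

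**3. Which outcomes are exposed?**
- *Open to judgement:* serious infectious events and relapse, both of which enter the log-rank comparisons; blood pressure, to a lesser degree.
- *Little or no room for judgement:* overall survival and BMI.
- *Recorded, but in no named comparison:* reasons for death. Statistical analysis does not describe a cause-specific analysis.
- *Separately protected:* the quality-of-life, fatigue, anxiety and depression questionnaires, given by blinded interviewers.

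**4. Does the sample size come into it?** Inputs from Sample size and Statistical analysis: difference 5, SD 7, two-sided alpha 5%, power 80%, 10% loss. By the normal approximation, n per arm = 2 × (1.96 + 0.84)² × 7² / 5² = 30.7, rounded up to 31. Then 31 / 0.9 = 34.4, rounded up to 35 per arm, or 70 in total, as stated. The calculation concerns the QLQ-C30 score and contains nothing about who records clinical status. Changing that leaves N, alpha and power as they are.

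**The case against.** The strongest reply is that hematologists follow these patients clinically and would often learn the arm anyway. HRVB patients attend 10 hospital sessions and practise daily at home until the 12-week follow-up, and the only non-disclosure request covers APA sessions, not medical visits. The affected outcomes are secondary, and the article openly declares hematologists unblinded, so readers can allow for it. This stands in part: it limits what blinding could achieve and lowers the importance of the point. It does not make the stated reason fit, and the interviewers, who face the same disclosure risk, are still to be blinded.

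A reader might also infer more than the document supports:

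- *That hematologists learn the arm only by randomising.* It is the only route described. Disclosure by patients remains open.
- *That one hematologist randomises and later assesses the same patient.* The text says variously a hematologist, the hematologist and the investigator. What it does establish is that hematologists as a group are unblinded.
- *That every clinical-status outcome is biased.* Overall survival and BMI are not materially exposed, and the article says the data are collected, not that they are adjudicated.
- *That a false-positive rate for blood pressure can be calculated.* The article gives no SD for blood pressure and no basis for the size of an observer's lean. The T3–T1 t-test is specified for questionnaire scores, cardiac coherence score and SDNN, not for blood pressure. Any such figure would mainly restate an assumed bias. The measuring device is not described either, so no criticism of it follows.
- *That hematologists could predict the next allocation.* The statistician's list, block sizes varying among 4, 6, 8 and 10, and allocation through the eCRF largely meet that worry.

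**Conclusion.** The concern holds in a limited form. The reason given for leaving hematologists unblinded applies to the APA instructor and does not by itself apply to them. The only described route to the arm, running the randomisation, can be reassigned. Knowledge of the arm among those who record serious infectious events, relapse and, to a lesser degree, blood pressure is therefore partly avoidable, and so is the detection bias it may bring.

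The document gives no basis for a numerical size, and none is claimed. The primary questionnaires, overall survival and BMI are not materially affected. The conclusion rests on two assumptions: that the condensed article correctly describes who does what, and that recording these outcomes leaves some room for judgement. It is a cheap improvement to secondary outcomes and does not threaten the primary comparison.

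**What to change.** 1. **Evaluation times and implementation, T1:** have the hematologist confirm eligibility and consent in the eCRF. Let the APA instructor, who is already unblinded, trigger the CsRandom step only after that confirmation is locked.
2. **Database and data monitoring:** hide the arm from the hematologist's eCRF role, using the role-based access already planned.
3. **HRVB training:** extend the request not to discuss the training to hematology visits.
4. **Blinding and intervention assignment:** confine the intervention-based reason to the instructor, and state that hematologists record clinical status blind to arm as far as possible.

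**Cost:** changed eCRF rights, an added line in the patient instruction, and short edits to the sections above. No extra staff are needed.

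**Downsides:** some patients will disclose, so blinding will be incomplete. A route for unblinding when needed must be kept. The instructor, who already books the T1 appointment, will also see allocations; locking eligibility and consent before the randomisation step limits that risk but does not remove it.

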## Methods/design

### Design and setting

The APACCHE protocol is a single-centre, parallel, randomized controlled superiority trial in adult hematologic patients who have been treated for hematologic malignancy in the hematology unit of the Hospital of Reunion Island, France. Modifications of this current protocol will have to be written as a protocol amendment by the Methodology and Data Management Centre and will have to be validated by the French ethical committee.

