### Study population

#### Inclusion criteria

Our study will include French-speaking patients, aged 18–70, with various forms of hematological malignancies, in post-treatment remission (full or partial) within the 6 months prior to the study, with stable hemoglobin levels (≥9 g/dl) and for whom APA is recommended by a hematologist. All patients will give their written informed consent.

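### The plan relies on investigators not knowing the block sizes, then prints the full set (4, 6, 8 or 10), which makes some allocations callable with confidence or certainty

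*Protocol article*

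**What the plan says.** The section Blinding and intervention assignment gives the purpose of the varying blocks: "Different sizes of randomization blocks will be used to leave the investigators blind to their size and to avoid predictable allocation". The sentence that follows is: "Randomized block sizes of 4,6,8 or 10 blocks will be performed on STATA". It gives the complete set of sizes, but neither their order nor their relative frequency.

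Other statements determine how exposed the sequence is:

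- Design and setting: "The APACCHE protocol is a single-centre, parallel, randomized controlled superiority trial in adult hematologic patients".
- Blinding and intervention assignment: "Randomization will be balanced in both groups, with a 1:1 allocation ratio, without stratification". There is therefore one sequence for all 70 patients. The same section says that the hematologists and the APA instructor cannot be blinded; only the questionnaire interviewers are. The statistician prepares the list and the investigator draws from it through the eCRF.
- Evaluation times and implementation, for T1: "the hematologist will obtain informed consent from the patients, and will proceed to the randomization".
- Inclusion criteria: patients must be those "for whom APA is recommended by a hematologist", so a hematologist's judgement is also part of eligibility.

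**The concern.** The article names a safeguard and then discloses the parameter on which it depends. If the people who enrol know the possible sizes, they can rule some out as a block unfolds and so become more confident about the next arm, sometimes certain.

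What is at stake is selection bias. If the coming arm can be foreseen, whom to approach, or when to randomize, can depend on it. Blinded interviewers protect the collection of quality-of-life scores, not the decision to enrol. Nothing in the article suggests that enrolment was steered; the point is that the stated protection is weaker than claimed.

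**Working it through.** **Inputs.** Block sizes 4, 6, 8, 10, ratio 1:1 and no strata (Blinding and intervention assignment); N = 70 (Sample size); one centre (Design and setting). Assumptions: each size has probability 1/4, and the guesser sees every earlier allocation.

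**The plan's own figure.** The article gives no number for predictability. Its N reproduces: 2 × (1.96 + 0.84)² × 7²/5² = 30.7, so 31 per arm; 31/0.9 = 34.4, so 35 per arm and 70 in total.

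**Step 1. Average guess rate, without using the sizes.** Always guess the arm that is behind, and toss a coin when level. For a block of 2m the expected number correct is m + (2^(2m)/C(2m,m) − 1)/2.

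| Block | Expected correct | Rate |
|---|---|---|
| 4 | 2 + (16/6 − 1)/2 = 2.83 | 70.8% |
| 6 | 3 + (64/20 − 1)/2 = 4.10 | 68.3% |
| 8 | 4 + (256/70 − 1)/2 = 5.33 | 66.6% |
| 10 | 5 + (1024/252 − 1)/2 = 6.53 | 65.3% |

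Over complete blocks: (2.83 + 4.10 + 5.33 + 6.53)/28 = 67.1%. Simulated lists cut at 70 give 66.8%, about 47 correct against 35 by chance. Two other weightings of the sizes give 66.9% and 67.5%. A Bayesian guesser who knows the sizes also scores 66.8%: the sizes add nothing to this average.

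**Step 2. What the sizes do add: confidence.** Suppose the first three patients go to the same arm. For size 2m this has probability proportional to (m − 2)/(2(2m − 1)), and the next patient then goes to the other arm with probability m/(2m − 3).

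- Sizes known: weights 0 (size 4), 0.100 (6), 0.143 (8), 0.167 (10); probabilities 1, 4/5 and 5/7 for sizes 6, 8 and 10. Result: (0.100 + 0.114 + 0.119)/0.410 = 81%.
- Sizes unknown, any even size from 2 to 20 equally likely: the same sum gives 0.947/1.400 = 68%.

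If the first five go to one arm, only size 10 is possible and the next five are certain.

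Over whole simulated trials of 70:

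| Guesser | Called at ≥ 75% | Certain |
|---|---|---|
| Knows 4, 6, 8, 10 | about 29% | 1.2% of allocations (0.86 per trial; at least one in about 26% of trials) |
| Supposes even sizes 2 to 20 | 0.6% | 0 |
| Supposes even sizes 2 to 12 | about 23% | 0 |

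The last row is a sensitivity check by the same calculation (6,000 lists). The gain in confidence depends strongly on what an uninformed guesser would suppose; the loss of certainty does not change between these two suppositions.

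**Step 3. Comparison with fixed blocks.** With a known fixed size, 32% of allocations are certain for blocks of 4 and 17% for blocks of 10. Varying the sizes has therefore removed most certain predictions even with the set printed.

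**Step 4. A less restrictive list.** Big-stick with tolerance 4 forces about 8.0 of 70 allocations. Its guess rate is 0.5 + 0.5 × 8.0/70 = 55.7%.

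**The case against.** **Is there a contradiction at all?** The article prints the set, not the current block's size, and Step 3 shows that variation still does most of its work. That stands, and makes the conflict partial. It does not remove it: the set alone produces the certain calls and many of the confident ones.

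**Do the printed sizes make two in three allocations guessable?** A reader might infer this from the two adjacent sentences. It is wrong. The 67% comes from small permuted blocks with unblinded sequential enrolment, and is the same with the sizes hidden.

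**Does the enrolling clinician see every allocation?** A reader might infer this too, but the article speaks of hematologists in the plural and does not say how many enrol or what each sees. If two clinicians each tracked only their own patients, the rate would be about 54%; for three, about 53%. The APA instructor, who supervises both interventions and arranges the T1 visit, is better placed to see the whole sequence, but does not run the randomization. So 67% is an upper figure.

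**Does the workflow blunt the risk?** Partly. APA is prescribed at T0 and randomization follows at T1, so others may be randomized in between. A guess made one allocation early is right about 60% of the time, two early about 57%. Consent and randomization do happen together at T1, so the fuller figure applies there.

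**Can the bias be put in points?** No. The article gives nothing on how patients chosen for one arm would differ, and it would have to be assumed that every enrolment was steered.

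**Should permuted blocks be replaced?** Not as a correction. Big-stick lowers the average guess rate but produces more allocations that are certain to anyone who knows the limit: about 8 per trial, against 0.86 now.

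**Conclusion.** The point holds in a limited form. The stated aim of hiding block size is undercut by the next sentence. For someone who knows the sizes and follows the whole sequence, about 29% of allocations can be called at 75% or better, and about one trial in four contains at least one certain allocation. Without the sizes, certain calls disappear and the confident share falls to about 1%, or only to about 23% if the guesser already supposes small blocks.

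These figures assume equally likely sizes and full sight of past allocations. The article does not say whether enrolling staff had the sizes while recruiting. The guess rate of up to 67% is a separate property of small blocks in an unblinded single-centre trial. It is not caused by the disclosure, and means that varying the sizes cannot by itself make allocation unpredictable.

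**What to change.** Have the statistician regenerate the unused part of the list with block sizes that are not disclosed. Keep those sizes only in a restricted file at the Methodology and Data Management Centre, and delete them from every document investigators see. Reword the purpose sentence so that it claims concealment of block size, not unpredictable allocation.

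The cost is one new list from the same statistician and an amendment. Start the new part at the end of a current block; a cut inside a block of 10 could leave an imbalance of up to 5. The sample size and analysis do not change. The change restores the stated concealment and removes the certain calls; it leaves the average guess rate where it is.

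If the team also wants a lower guess rate, a big-stick list is an optional trade-off. Tolerance 4 gives about 56% correct guesses, at the price of about 8 forced allocations per trial and final arms that may differ by up to 4 (33 against 37). Its limit would have to be kept just as confidential.
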